#### Data sources

The YETI Partner Study will use a combination of EHR and questionnaires to collect data.

EHR data will include HCV testing, treatment initiation, completion, and cure information, which is requested every 3 months for Index participants via medical record number (MRN).

Self-report data will be collected individually through staff-administered questionnaires at the baseline screening visit, after informed consent, and all subsequent visits.Data will be collected individually and in separate rooms for the Index and Partner participants to ensure accurate responses. Questionnaires will assess the following domains:Demographic characteristics will include age, gender, sexual orientation, race/ethnicity, education level, employment status, sources of income, food security using the USDA Household Food Security Survey Model, and living arrangements.Healthcare access characteristics will include access to providers, emergency care, and barriers to access.HCV knowledge will be measured using an adapted HCV Knowledge questionnaire from the Canada Treatment Information Exchange (CATIE).Drug use questions will cover methods, frequency, and substances used, equipment sharing and harm reduction practices, attitudes towards current use, receipt of opioid substitution therapy, overdose, and alcohol and tobacco use. These measurements have been adapted from questions employed by the PIs.Partner and relationship characteristics will be measured using information about partner dynamics, social networks, injecting dynamics, and partner support via the 54-item IDIP scale [32], the Source-Specific SPS-24 [39], and the SPS-24 adapted for HCV treatment initiation.Police interactions will include interactions with police and history of incarceration or parole.General health includes HCV history, quality of life, and depression. Depression will be measured using the standardized Center for Epidemiologic Studies Depression Scale (CESD) [40].Stigma and racism will be captured using the Substance Use Stigma Mechanisms Scale (SU-SMS) [41] with adaptations and the Experiences of Discrimination scale with minor adaptations in language [42].

Subsequent visits will include questions related to the Index’s and Partner’s experiences with the intervention and self-reported outcome data.

#### Plans to promote participant retention and complete follow-up {18b}

See {11c}.

The study incorporates several strategies rooted in our experience working with PWID and conducting dyad studies to maximize participant retention. Subsequent visits will be scheduled immediately after completion of the current visit. Using regularly updated contact information, study outreach workers will maintain participant contact via e-mail, text messaging, phone calls, and visiting frequented street locations. Participants will receive cash payments on a flat scale at each visit. However, dyads will be provided a higher cash incentive if they present for a visit at the same time. To expand study outreach, we will provide CBO partners with a list of participants with outstanding visits monthly.

#### Data management {19}

The YETI Partner Study will employ standardized procedures for data entry, coding, security, storage, and analysis to ensure data quality and confidentiality. Data will be entered electronically into REDCap, a secure and UCSF-approved database. The database will include close-response entries and range restrictions to maximize valid data entry. Critical data points will undergo double data entry by different team members, with discrepancies resolved through a third review at regular intervals. Automated range checks will ensure data values fall within expected ranges. Data will be entered in real-time during participant visits to reduce recall bias.

Each participant and dyad will be assigned a unique study ID number to anonymize data. Data will be coded using standardized protocols, including demographic information, health status, and questionnaire responses. All electronic data will be stored on secure, password-protected servers with restricted access, maintained by UCSF’s IT department. Physical documents will be stored in locked filing cabinets accessible only to authorized study personnel and shredded after digitization. Data linking participant identities to their study IDs will be kept in a separate, secure file with limited access. All study personnel will undergo mandatory HIPAA and privacy training.

Data will be transferred into RStudio or STATA and cleaned before analysis using the most current version. The dataset will be locked, and all analyses will be performed by the study’s biostatistician as well as study team members, and collaborators in conjunction with guidance from the biostatistician and principal investigators (PIs) while blinded to study allocation. Regular audits of data quality and completeness will be conducted monthly by a research assistant and reviewed quarterly by the PIs. Compliance with data management protocols will be ensured through regular training sessions and detailed documentation. Further details of the data management procedures are available in the study protocol.

#### Confidentiality {27}

All collected information will be kept strictly confidential and stored in accordance with national regulatory approvals. The PIs and biostatistician will be the only study personnel with access to the code list.

#### Plans for collection, laboratory evaluation and storage of biological specimens for genetic or molecular analysis in this trial/future use {33}

See above 26b—this trial does not involve the collection or storage of biological specimens. As such, there are no provisions or protocols for their handling within this study.

## Statistical methods

### Statistical methods for primary and secondary outcomes {20a}

A detailed plan for analysis will be developed before data extraction, but some of the principles of data analysis are outlined here. Analysis will be reported in accordance with the Consolidated Standards of Reporting Trails (CONSORT) statement [43]. All analyses will be performed by the study’s biostatistician as well as by select team members under the guidance of the study’s biostatistician and the PIs. All trial data will be summarized by treatment group.

Randomization should result in a balance on covariates across the intervention and control groups. In the unlikely event that imbalance is detected across groups on one or more of the demographic variables, we will use methods based on the Rubin causal model (e.g., propensity scores, double-robust estimation) to obtain intervention effect estimates under the counterfactual assumption of balanced groups.

Our primary analysis will follow an intention-to-treat (ITT) approach with no account taken of protocol non-adherence. We will address incomplete data via direct maximum likelihood estimation (MLE) or multiple imputation (MI), which make the relatively mild assumption that incomplete data arise from a conditionally random (MAR) mechanism. Auxiliary variables will be included to help meet the MAR assumption and sensitivity analyses will be conducted with controlled MI or other relevant methods to assess the robustness of the MAR assumption [44]. Well-tested commands and procedures in the statistical program R or STATA will be used to perform the descriptive and mixed models analyses planned to address questions of the mechanism of action. The specialized latent variable modeling program M*plus* will be used to fit secondary exploratory mediation and moderation analyses. All program code will be documented extensively to enable future code review, transparency, and results reproducibility.

Given the randomized design, the primary comparison will include the cumulative incidence and risk ratios with 95% CI for HCV treatment initiation by Index participants at 6 months post-enrollment and across the entire follow-up period by randomization group. We will use a survival framework that acknowledges loss to follow-up with at-risk time beginning at study enrollment and censoring at the date of the final attended follow-up visit. The event of interest is HCV treatment initiation using a known or self-reported date of HCV treatment initiation.

Secondary analyses will include comparisons of other treatment completion and SVR12 by randomization group, with subgroup analyses for a stratum of Index ≤ 30 years of age, gender, race, and ethnicity.

While all Index participants will be living with untreated HCV at the time of study enrollment, some injecting partners will also have untreated HCV infection and may benefit from intervention involvement. Exploratory analyses will measure differences in the probability of initiating HCV treatment for HCV-infected partners by randomized group.

An exploratory linear mixed model (LMM) will assess the putative mechanisms of action by which changes in partner support and interpersonal factors (over time and by group) impact HCV treatment initiation.

Additional secondary exploratory analyses with intact dyads where both partners have data on the same independent variables will enable the investigation of partnership-based research questions that explore how relationship dynamics affect behavior change in partnerships. Therefore, we will extend the mixed models described above to include actor and partner effects for the continuous partner support variables. This technique illuminates the effects that partners in injecting partnerships can have on both their own and their partner’s behavior. Estimation of separate actor and partner effects will enable us to use contrasts to test whether partner effects are greater in magnitude than actor effects. α will be set at 0.05 for these exploratory analyses.

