### Sample size {14}

The primary superiority hypothesis for this trial, that those randomized to the intervention will have a higher 6-month probability of treatment initiation compared to those in the control group, was powered based on our previous work and comparable results of community-based RCT studies with PWID that suggest a HCV treatment initiation rate of 30% for those in the intervention group (13% in control group), and a retention rate of 80% (based on our previous cohort of injecting partnerships) [37, 38]. We will have 80% power to detect this effect with a sample size of 250, corresponding to a risk ratio of 2.0, at the 5% significance level.

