## Assignment of interventions: allocation

### Sequence generation {16a}

The sequence of random assignments will be generated and uploaded into REDCap for use with enrollment. A simple randomization allocation table will be generated using sorted random values to distribute allocation to the intervention or control arm. This will allow for concealment allocation as research staff will not be able to anticipate allocation.

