### Methods for additional analyses (e.g., subgroup analyses) {20b}

Subgroup analyses will be performed to examine differences in outcomes across various participant characteristics, such as age, gender, and baseline HCV status. Adjusted analyses will account for potential confounders and covariates, such as socioeconomic status, healthcare access, and injecting network size.

To address specific hypotheses, LMMs and generalized linear mixed models (GLMMs) will be employed. LMMs will be used to assess continuous outcomes, such as interpersonal factors and partner involvement levels, with repeated measures for each participant within dyads. GLMMs will be used to evaluate binary outcomes, such as HCV treatment initiation, incorporating random intercepts to account for clustering within dyads. Exploratory analyses will include mediation and moderation analyses to investigate the mechanisms through which the intervention affects outcomes and to identify factors that may influence the strength or direction of these effects.

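### Adjustment for demographics hangs on an observed imbalance called unlikely, yet with nine demographic domains and simple randomization a 5% check would find one in about 27–37% of trials

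*Protocol article*

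**What the plan says.** All references are to the protocol article.

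- **Statistical methods {20a}**, the rule: "In the unlikely event that imbalance is detected across groups on one or more of the demographic variables, we will use methods". The methods are then described as "methods based on the Rubin causal model (e.g., propensity scores, double-robust estimation) to obtain intervention effect estimates", given as examples.
- **Statistical methods {20a}**, the primary comparison: cumulative incidence and risk ratios by randomized group, at 6 months and over all follow-up, in a survival framework that censors at the last attended visit. No covariates are named. The primary analysis is by intention to treat.
- **Data sources**, the variables that the trigger would inspect: "Demographic characteristics will include age, gender, sexual orientation, race/ethnicity, education level, employment status, sources of income, food security", followed by living arrangements. That makes nine domains. Healthcare access is listed separately.
- **Sequence generation {16a}**: "A simple randomization allocation table will be generated using sorted random values". No stratification or blocking is described.
- **Methods for additional analyses {20b}**, with no imbalance trigger: "Adjusted analyses will account for potential confounders and covariates, such as socioeconomic status, healthcare access, and injecting network size".

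**The concern.** Under correct randomization, any baseline difference between the arms is due to chance. A rule that adjusts when a difference is seen therefore selects variables by accident. Whether a variable is worth adjusting for depends on how well it predicts treatment initiation, and a balance check says nothing about that. The rule also looks at demographics alone.

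Two things are at stake. First, the reported effect can depend on which variables happened to differ. The document describes three routes to an effect estimate: unadjusted by group, causal-model adjustment if triggered, and adjusted with an open list of other covariates. It does not rank them. Second, precision that a fixed set of prognostic covariates would give in every trial is left to chance. Calling the trigger unlikely hides how often it would operate.

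**Working it through.** **The plan's own figure.** The document gives no probability of imbalance, only the word unlikely. Its sample size does reproduce. For 30% against 13% at a two-sided 5% level with 80% power, the continuity-corrected formula gives 102 per arm, so 204 in total, and 204/0.8 = 255 after allowing for 80% retention, close to the stated 250. With 100 retained per arm, exact (Fisher) power is 80.0%. The expected number of initiations among those retained is 100 × 0.30 + 100 × 0.13 = 43, which limits how many covariates the model can carry.

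**How often the trigger fires.** There are nine domains (Data sources). The level of each check is not stated. The article gives 5% only for the primary test ("at the 5% significance level"), so 5% per variable is an assumption. If the checks are independent:

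P(at least one) = 1 − (1 − α)^k = 1 − 0.95^9 = 0.370

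| Assumed rule | P(at least one imbalance) |
|---|---|
| 9 variables, 5%, independent | 37% |
| 9 variables, 5%, correlation 0.2 | 35% |
| 9 variables, 5%, correlation 0.3 | 33% |
| 9 variables, 5%, correlation 0.5 | 27% |
| 5 variables, 5%, independent | 23% |
| 12 variables, 5%, independent | 46% |
| 9 variables, 10%, independent | 61% |
| Standardized difference > 0.25, 125 per arm | 36% |
| Standardized difference > 0.2, 125 per arm | 66% |
| Standardized difference > 0.1, 125 per arm | 99% |

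The correlated rows come from simulation. The last three rows use P = 2[1 − Φ(t/√(2/125))] for each variable. For t = 0.1 this is 0.429, and 1 − 0.571^9 = 0.99.

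**What the trigger costs.** Two simulations compared no adjustment, adjustment only if imbalance is detected at 5%, and fixed adjustment. All prognostic strengths are assumed, because the document gives none. The alternative is 30% against 13%.

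*Simulation 1:* 250 participants and nine independent covariates, each with the log-odds per SD shown.

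| Strength | Type I error: unadjusted / fixed / conditional | Power: unadjusted / fixed / conditional |
|---|---|---|
| 0 | 5.5 / 5.4 / 5.4% | 91.4 / 90.4 / 91.0% |
| 0.2 | 4.5 / 4.5 / 4.5% | 90.7 / 90.7 / 90.7% |
| 0.4 | 4.8 / 4.9 / 4.5% | 83.3 / 88.2 / 85.0% |

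At strength 0.4 the conditional rule recovers (85.0 − 83.3)/(88.2 − 83.3), about one third of the available gain.

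*Simulation 2:* 100 per arm. Two demographics have log-odds of 0.4 to 0.5 per SD, and two other baseline variables 0.5 to 0.7. Type I error was about 5% throughout. Power was about 85% unadjusted, 84.6% with the conditional rule and 87.6 to 89.5% with a fixed set of the four, a difference of 3.0 to 4.9 points from the conditional rule. Part of this gain comes from including the two non-demographic predictors, which the trigger never considers.

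**The case against.** Several stronger readings are tempting, and the document does not support them.

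- **That the primary estimator is replaced after the data are seen.** A reader might infer this, but {20a} never says that the causal-model estimate displaces the comparison by randomized group. It may be meant as a supplement. What stands is that the document does not say which.
- **That adjustment happens only if the trigger fires.** Section {20b} plans adjusted analyses without any trigger and names healthcare access among the covariates. These are additional analyses with an open list, so they do not settle the primary estimator.
- **That the rule inflates false positives.** Neither simulation shows this. The choice would rest on baseline data, not outcomes, and analysts are to be blinded to allocation.

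The 37% is also not a property of the plan. It needs nine independent checks at 5%, and education, employment, income, food security and living arrangements are plausibly correlated. A stricter rule fires less often: at 1% per variable, 1 − 0.99^9 = 8.6%, and unlikely would then be fair. The article states no such rule.

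Finally, a detailed analysis plan is to be written before data extraction. The threshold, the choice between methods and the covariate list could properly be set there, and their absence here is not a fault. But the article gives the trigger as a principle of the analysis, so a later plan would inherit it. The objection here is to the principle.

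**Conclusion.** The point holds in limited form. The article states a rule that selects adjustment variables by chance difference and calls its own trigger unlikely. With nine domains, simple randomization and an assumed 5% check, the trigger would operate in about 27–37% of correctly conducted trials, and in up to 99% under a standardized-difference rule of 0.1. The standing of the triggered estimate relative to the primary risk ratio is not stated.

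The consequence is modest. Validity is not threatened. Compared with the conditional rule, fixed adjustment changes power by between about nothing and 5 points, depending wholly on how prognostic the covariates are. If they predict nothing, fixed adjustment for all nine costs about one point against no adjustment (91.4% to 90.4%). This is worth correcting because it is cheap and recruitment is expected to run to December 2027. It is not a flaw that undermines the trial.

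**What to change.** In {20a}, delete the imbalance trigger and the word unlikely. In their place, state:

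1. One primary estimator of the 6-month risk ratio, adjusted whatever the observed balance for a short fixed list of prognostic baseline variables. With about 43 expected events, two to four is reasonable, for example age, housing and healthcare access, all within the domains already collected.
2. That each listed variable is recorded before allocation or cannot be affected by it. This needs care, because {18a} places the enrollment questionnaire after randomization. Age is safe in either case. Self-reported healthcare access should be asked before the arm is known.
3. An estimation method that fits the survival framework and its censoring, such as covariate-adjusted, standardized cumulative incidence with bootstrap confidence intervals. A plain binary regression at 6 months would not handle the censoring.
4. That the unadjusted risk ratio is reported beside it, and that the adjusted analyses in {20b} are supportive.

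The cost is mainly wording, plus confirming or moving the timing of a few baseline questions. The list must be fixed before data extraction. If the chosen variables turn out not to be prognostic, there is little or no gain, and about one point of power lost at worst in the simulations.

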#### Trial design {8}

The *Y*ou’re *E*mpowered for *T*reatment *I*nitiation (YETI) Partner study is a non-blinded, parallel-group, two-arm, superiority randomized controlled trial with 1:1 allocation ratio to assess the efficacy of a two-session dyadic intervention to involve injecting partners as peer navigators to HCV treatment.

We aim to recruit and randomly allocate 250 persons living with HCV (“Index participants”) and their primary injecting partners (“Partner participants”) to either a control or intervention group. The primary endpoint is starting HCV treatment; secondary endpoints are treatment completion and sustained virologic response at 12 weeks post-treatment completion (sustained virologic response 12 weeks post-treatment, SVR-12). A description of the overall study design is in Fig. 1 and the schedule of enrollment, interventions, and assessments is in Fig. 2. Eligible PWID with evidence of HCV infection who enroll will be randomized (1:1) to either a control or intervention group. Both Index and Partner participants will participate in all five study visits: baseline (visit 1), 1-week (visit 2), 1-month (visit 3), 4-month (visit 4), and 7-month (visit 5). Questionnaires will be administered to the Index and Partner at all five visits. Intervention session 1 will be administered with the Index participant only at visit 1, and intervention session 2 with both the Index and Partner participants at visit 2. To expand our ability to capture primary endpoint data, participant data will be linked to their electronic health record (EHR) for HCV treatment start date, completion date, and SVR-12. The study protocol (version 1.4, 03/21/2024) follows the Standard Protocol Items: Recommendations for Interventional Trials (SPIRIT) Statement. The trial has been registered at ClinicalTrials.gov (ID: NCT06179498).

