### Who will take informed consent? {26a}

#### Written consent to participate

Eligible participants (Index and Partner) who present in-person at the study site for visit 1 will individually undergo a fully informed written e-consent protocol led by trained study staff. Research participants should be able to understand, as completely as possible, what procedures, risks, benefits, alternatives, and rights are involved, and make an informed choice about being in the study without pressure or undue inducement to participate.

During this process, consent will be requested for (a) study participation and (b) the release of medical records for up to 5 years post-participation. To help protect our participants’ privacy, we have received a Certificate of Confidentiality from the National Institute of Health. Our consent form and plain language companion document, approved by the IRB at our university, were developed in partnership with members of our community-academic partnership through a series of group discussions focused on improving readability and transparency. Directly after voluntary consent is obtained and documented on REDCap, participants will begin visit 1. REDCap (Research Electronic Data Capture) is a secure, web-based software platform designed to support data capture for research studies, providing (1) an intuitive interface for validated data capture; (2) audit trails for tracking data manipulation and export procedures; (3) automated export procedures for seamless data downloads to common statistical packages; and (4) procedures for data integration and interoperability with external sources [35, 36]. Study data were collected and managed using REDCap electronic data capture tools. Those who decline study enrollment will receive information about HCV prevention strategies and HCV treatment resources and will be paid $5 for their time.

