### Outcomes {12}

The primary outcome of this trial will be the initiation of HCV treatment within the study period. Secondary outcomes will include (a) completion of HCV treatment; and (b) achievement of SVR12. All outcomes will be measured within 2 years of enrollment. Individuals without evidence of an HCV-associated visit or without indication of DAA treatment prescribed will be considered to have not started HCV treatment. Outcomes will be assessed using data from questionnaire responses and EHR integration.

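### The primary analysis censors at the last attended visit, although treatment starts are obtained from health records whether or not the participant attends

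*Protocol article*

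**What the plan says.** Statistical methods {20a} defines the primary comparison as cumulative incidence and risk ratios for treatment initiation at 6 months and over all follow-up, "with at-risk time beginning at study enrollment and censoring at the date of the final attended follow-up visit". It adds: "The event of interest is HCV treatment initiation using a known or self-reported date of HCV treatment initiation". It gives no rule for a start dated after the last attended visit.

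Other sections of the Protocol article describe ascertainment that does not need a visit:

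- Trial design {8}: "To expand our ability to capture primary endpoint data, participant data will be linked to their electronic health record (EHR) for HCV treatment start date".
- Data sources: record data on Index participants, including treatment initiation, are requested every 3 months by medical record number.
- Written consent to participate: consent is sought for "the release of medical records for up to 5 years post-participation".
- Outcomes {12}: "All outcomes will be measured within 2 years of enrollment". The same section classes people with no evidence of treatment as not having started, which makes them non-events and not censored observations.

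Visits take place at baseline, 1 week, 1 month, 4 months and 7 months.

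**The concern.** Record linkage means that an Index participant who stops attending can still have an observed outcome. The censoring rule gives that up. It can be applied in two ways, and each has a fault.

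- **Strict reading.** A recorded start after the last visit is not counted. Known outcomes are thrown away, and the estimate then rests on the assumption that people who stop attending would have started treatment at the same rate as attenders. The records make that assumption largely unnecessary.
- **Loose reading.** A recorded start after the last visit is counted, but a non-starter leaves the risk set at the last visit. Everyone followed past dropout is then someone with the event, so cumulative incidence is overstated even when dropout is random. The size of the error depends on each arm's attendance.

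Participants and visit staff are unblinded and the intervention is delivered at visits 1 and 2, so attendance could differ by arm and track engagement in care. Choosing between the readings after the data are seen would be a discretionary decision on the primary endpoint.

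The rule also ends follow-up at 7 months even for a full attender, about 17 months before the two-year outcome window closes (24 − 7 = 17).

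**Working it through.** **Inputs from the Protocol article.** Sample size {14}: 30% against 13% initiation, 80% retention, N = 250. Visit times are as listed above.

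**Assumptions not in the document.** Start times have a constant hazard. Last visits of those lost are spread evenly over visits 1 to 4. Every start is found in the records. Retention by arm is not given, so a range is shown.

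**The plan's own sample size.** For 13% against 30%, two-sided 5% and 80% power, the continuity-corrected formula gives 102 per arm, 204 in total, and 204/0.8 = 255, close to 250. With 250 × 0.8 = 200 retained (100 per arm), power is 80.0% by Fisher's exact test. The inputs are therefore understood correctly. The risk ratio they imply is 30/13 = 2.31, which is used below.

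**Share of six-month starts dropped under the strict reading.** Hazard λ = −ln(1 − p)/6 per month, S(v) = exp(−λv), and share = 0.2 × mean over v of [S(v) − S(6)] / p, for v = 0, 0.25, 1 and 4 months.

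- Control: λ = 0.0232. S(v) = 1, 0.994, 0.977, 0.911 and S(6) = 0.870. Mean difference 0.1007; 0.2 × 0.1007/0.13 = 15.5%.
- Intervention: λ = 0.0594. S(v) = 1, 0.985, 0.942, 0.788 and S(6) = 0.700. Mean difference 0.2290; 0.2 × 0.2290/0.30 = 15.3%.

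If the hazard halves after loss, simulation gives about 9%.

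**Simulated Kaplan-Meier risk at 6 months** (at least 10^6 participants per arm; retention shown as intervention/control; records to 6 months):

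| Scenario | True RR | Strict RR | Loose RR |
|---|---|---|---|
| 80/80, same rate after loss | 2.31 | 2.30 | 2.24 |
| 80/80, half the rate after loss | 2.32 | 2.30 | 2.28 |
| 85/75, same rate after loss | 2.30 | 2.31 | about 2.08 |
| 85/75, no effect | 1.00 | 1.00 | 0.92–0.93 |
| 90/70, half the rate after loss, overall risk held at 13% in each arm | 1.00 | 0.92 | 0.84 |
| 90/70, half the rate after loss, equal hazard before loss | 1.08 | 1.00 | 0.91 |

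In the first row the loose reading gives risks of 15.1% and 33.8% against true risks of 13.0% and 30.0%. With records to 2 years it gives 14.3% and 31.2%, RR 2.18. In the second row the true risks are 12.0% and 27.9%, and the strict reading returns 13.0% and 30.0%.

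The last two rows differ only in what is held equal between arms. The relative error is the same to rounding: strict 0.92 and 1.00/1.08 = 0.93; loose 0.84 and 0.91/1.08 = 0.84.

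**Following everyone to the record horizon** recovers the true risks in every scenario.

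**Precision.** If no Index participant lost the primary outcome, 125 per arm would give 91.0% power against 83.8% at 100 per arm without continuity correction, or 88.2% against 79.1% with it. These gains are upper limits, because a survival analysis already uses the partial follow-up of those lost.

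**The case against.** There is a fair case that the practical effect is small.

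- The only retention figure is 80% overall. With equal retention the risk ratio moves from 2.31 to 2.30 (strict) or 2.24 (loose). The larger shifts need a difference between arms that no passage supports, and incentives and tracing are the same in both arms. **This stands.** Those rows are conditional, and the direction is unknown: swapping the retention figures in the 85/75 no-effect row would give about 1/0.93 = 1.08.
- The timing of loss is assumed. If all those lost were last seen at 4 months, the strict reading drops about 6% (control: 0.2 × (0.911 − 0.870)/0.13 = 6.3%), and the loose reading gives about 32% and 14%. **This stands** as a limit on the size.
- Dropping known events is not bias in itself. Strict Kaplan-Meier is unbiased when dropout is unrelated to starting treatment. **This stands**, but it is the assumption that the records would largely remove.
- The plan has multiple imputation or maximum likelihood and sensitivity analyses for missing data. **This does not answer the point.** Those methods address outcomes that were not observed, while the rule sets aside outcomes that were.
- Outcomes {12} counts people without evidence of treatment as not started, so neither reading need arise. **This shows a second conflict**: the same untreated dropout is a non-event in one section and censored in another.
- The six-month hypothesis lies within the visit schedule, so the two-year mismatch affects only the whole-follow-up comparison and time to initiation. **This stands.**
- Records may miss treatment given outside the linked systems. **This stands**, and the fix must allow for it.

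**Conclusion.** The concern holds. The article states a definite censoring rule for the primary analysis, and that rule conflicts with how and for how long the outcome is ascertained. It is not a detail left to a later analysis plan.

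At the plan's own inputs the cost under the strict reading is about 15% of six-month starts (6% to 15% across the timing and post-loss rates examined, apart from still lower post-loss rates). Under the loose reading absolute risks are overstated by about 2 and 4 percentage points. The risk ratio is little affected if retention is equal. It is distorted by roughly 8% to 16% in the 85/75 and 90/70 scenarios, in a direction that depends on which arm attends better.

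These sizes rest on the assumed hazard, timing of loss and retention split. That the primary estimate depends on visit attendance does not rest on them.

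**What to change.** Replace the censoring sentence in Statistical methods {20a} with a rule along these lines:

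- For Index participants with a linked record, count every documented start. Censor at the earliest of the analysis horizon, the last record data cut, death, or withdrawal of consent to record release, irrespective of visit attendance. The horizon is 6 months for H1a and a stated later time for H1b.
- For Index participants without a linkable record, censor at the last attended visit.
- Report last-visit censoring for everyone as a sensitivity analysis. Starts known only from self-report depend on attendance and a silent record may not be a true non-start, so this comparison shows how much either matters.

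Outcomes {12} should be aligned so that it says the same thing about people without evidence of treatment. The final record request must cover each participant's full horizon.

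The cost is one sentence in the analysis section and a matching edit in Outcomes {12}. The record requests and the consent for record release are already in place, and no sample size change is needed.
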